### Interventions

This study will be performed to compare a neck-strengthening exercise protocol with a sham ultrasound group in migraine subjects. In both groups, there will be a combination of home stretching exercises. The interventions in both groups will last for 2 months. After completion of treatment, patients of both groups will be followed up by phone at 1, 2, and 3 months.

Intervention group (IG): the 8-week exercise program to be used in this study will be based on the protocol described by Falla et al. [28], which consists of specific exercises to strengthen the flexor and extensors muscles of the neck. Participants will receive instructions and guidance from a trained therapist for 30 min once a week. The protocol consists of two stages:
*Stage 1:* The first stage, of 6-week duration, will focus on incremental craniocervical flexion in a relaxed, supine position and craniocervical extension, flexion, and rotation in a prone-on-elbows position while maintaining the cervical spine in a neutral position (Fig. 2) [28]. The initial proposal for the deep flexors and extensors of the cervical spine will be 2 sets of 10 repetitions. However, for the deep flexor muscles, the movement should be initially sustained for 10 s. If the participant cannot perform the targeted program, the number of sets, repetitions, and time of sustentation (for the deep flexors) will be redefined. According to the tolerance of the patient, the sets, repetitions, and time of sustentation will be increased weekly [28].*Stage 2:* The second stage, of 2-week duration, consists of both flexor and extensor exercises with higher load, using head weight as the load [28]. A neck flexion associated with a head flexion will be performed with the participant in the supine position, removing the head from the stretcher. For the extension exercise, while performing the neck extension the patient will be instructed to maintain the cervical spine in the neutral position, and the body in the position of 4 supports (Fig. 3). Each of the exercises will be for 3 sets of 15 repetitions at a time over the course of 2 weeks [28].

**Fig. 2 Fig2:**
[figure not shown]
First stage of neck-specific exercise program

**Fig. 3 Fig3:**
[figure not shown]
Second stage of neck-specific exercise program

Participants will be instructed to perform the same exercises at home, twice a day, for 10–20 min a day. They will receive a guideline book containing a neck-specific exercise program, including neck muscle stretching exercises.

Sham ultrasound group (USG): participants in this group will have meetings once a week for 8 weeks. The application of disconnected of therapeutic ultrasound (US) will be performed bilaterally in the middle portion of the upper trapezius. The application time will be around 9 min for each side, totaling approximately 20–25 min per session. Participants will also receive a guideline book, containing only cervical spine stretching exercises.

### Outcomes

The primary outcomes of this study will be the frequency and intensity of migraine. The frequency of headache attacks data will be collected by means of the headache diary, which will be delivered monthly to the patient. The frequency of migraine will be computed and analyzed in terms of days-of-pain per month. The migraine intensity will be also collected in the headache diary. The volunteers will classify the pain according to the numerical pain scale (NPS; 0–10) [32], and for the analysis of these data an average will be used. The secondary outcomes will be as follows: global perception of change, migraine-related disability, neck pain, cervical range of motion, pressure pain thresholds, muscle performance, observed by muscular strength, the cranio-cervical flexion test (CCFT), and the endurance of cervical musculature, in addition to the electromyographic parameters used in these tests.

### Process variable

All volunteers will meet weekly with the responsible therapist. During all meetings, the therapist will ask, and note, if the volunteers: are doing the home care. If volunteers get additional care, the therapist will be informed and this information will be noted. As well as the use of non-prescribed medications.

### Data collection

All data, except the electromyographic signals, will be collected and noted by the evaluators on paper records specific to the evaluations. Electromyographic data, in turn, will be collected and automatically stored in individual file folders in a computer used exclusively for the study. After the conclusion of the data collection, the data will be transcribed into Excel® spreadsheets by an examiner not involved with the data collection or treatment, using codes to preserve volunteer identification. The frequency and intensity of migraine attacks will be recorded in paper-pain diaries. After 30 days, the diaries will be given to the therapist responsible for the collections to transcribe the data into Excel® spreadsheets (Fig. 1).

### Methods for data collection

#### Questionnaires

*Neck Disability Index* (NDI): a valid instrument with good responsiveness [33], is the most recommended means to evaluate the functional disability associated with neck pain [34].*Migraine Disability Assessment* (MIDAS): a valid and reliable questionnaire used to assess the functional disability related to migraine [35, 36].*Tampa Scale for Kinesiophobia* (TAMPA): a 17-item scale originally developed to measure the fear of movement related to chronic lower back pain; however, it is also used to measure the fear of movement in different parts of the body and presents a good applicability psychometric for the cervical region [37].*Patient-Specific Functional Scale* (PSFS): a valid, reliable, and sensitive scale used to assess functional changes over time in patients with musculoskeletal disorders [38].*12 item Allodynia Symptom Checklist* (ASC-12): a reliable instrument to determine the presence and severity of cutaneous allodynia [39].*Global Perception of Change:* a one-dimensional scale in which individuals rate their improvement associated with an intervention on a scale of seven items [40].

#### Cervical range of motion

The cervical range of motion for flexion, extension, lateral-flexion, and rotation of the neck will be performed using the Cervical Range of Motion (CROM) (Performance Attainment Associates, Roseville, MN, USA). Two trials of each movement will be performed with the volunteer in a chair in their usual sitting position [22].

#### Pressure pain thresholds

Pressure pain thresholds will be assessed by using a digital manual dynamometer (DDK-10 Kratos®). A pressure of approximately 0.5 kg/cm^2^/s will be applied, with optimal positioning of the device perpendicular to the evaluated anatomical surfaces [24]. In addition, a digital metronome with a frequency of 1 Hz will be used to provide audio feedback and standardization of the pressure application speed [41]. Pressure pain threshold will be assessed randomly and repeated twice, bilaterally, over the upper trapezius, the sternocleidomastoid, the suboccipital, temporal, frontal, and levator scapulae [24, 42–44].

#### Craniocervical flexion test (CCFT)

The muscular performance of the cervical deep flexors will be evaluated by using the CCFT, a neuromuscular low-load test used to evaluate the activation and endurance of the deep flexors [45]. The test is performed with the subject supine with a pressure biofeedback unit (Stabilizer, Chattanooga, South Pacific; USA) placed behind the neck and inflated to 20 mmHg. The subject is instructed to perform a gentle and slow head-nodding action of craniocervical flexion over five incremental stages of increasing range (2 mmHg at each stage), with each stage maintained for 10 s. Subjects will perform two repetitions of 2 s at each stage in order to familiarize themselves with the task. During this familiarization test, signs of inappropriate performance, such as head retraction, head lift, or difficulty relaxing after the contraction are discouraged. Subjects then perform the CCFT holding the target level for 10 s with a 30 s rest period between levels without any control of potential compensations. The test is interrupted following the identification of any compensation, such as simultaneous palpable contraction of superficial flexors, and the latest stage performed without any compensation, will be registered as the targeted level [45].

#### Muscle strength during the maximal isometric voluntary contraction (MIVC)

The measurement of muscle strength during a MIVC will be performed according to the protocol described by Carnevalli et al. [46] A manual dynamometer attached to a non-elastic belt will be used (Lafayette Instrument Company®, model: 2201163, Lafayette, IN, USA). For measurement of flexion force, the patient will be placed in the supine position and will have their pelvis and trunk stabilized by non-elastic belts; the dynamometer will be positioned in a midline on the frontal bone. The measurement of cervical extensor strength will occur with patients in the prone position and stabilization at the same points as the flexor test; the dynamometer will be positioned in a midline over the occipital bone. For both measurements, 3 trials will be performed with contractions sustained for 3 s. Rest of 30 s will be allowed between repetitions, and 2 min between muscle groups (Fig. 4).

**Fig. 4 Fig4:**
[figure not shown]
Muscle strength during the maximal isometric voluntary contraction. (**a**) cervical flexors; (**b**) cervical extensors

#### Endurance test of flexor and extensor muscles of the cervical spine

To verify the endurance of the cervical flexor muscles, subjects will be placed in the supine position with their head resting on the hand of the therapist in a neutral position. At the beginning of the test, the volunteer should perform a head and neck flexion by lifting their head up from the stretcher; the holding time will be registered in seconds and only one repetition will be performed. The test will be interrupted if the therapist notes the presence of pain or fatigue, or if the head of the volunteer touches the hand of the therapist [47]. For the neck extensors, the volunteer will be placed in a prone position with the head resting on a removable support of the stretcher; stabilization will occur at the T6 level by a non-elastic belt. To measure the degrees of displacement of the head a CROM device will be used and a weight of 2 kg will be added, attached to a non-elastic band positioned on the head of the patient. The support will be removed, and the patient should keep their cervical spine in the neutral position. The holding time will be registered in seconds and only one repetition will be performed. The test will be stopped in case of pain, fatigue, or if the head inclination varies more than 5° (Fig. 5) [47].

**Fig. 5 Fig5:**
[figure not shown]
Endurance test of flexor (**a**) and extensor (**b**) muscles of the cervical spine

#### Surface electromyography

Activation of the cervical muscles will be recorded by surface electromyography during the CCFT, MIVC, and muscle endurance test. Wireless surface sensors (TrignoTM Wireless System, Delsys Inc., Boston, MA, USA) will be firmly fixed with adhesive tape, bilaterally over the following: 1, sternal head, 1/3 distal of the muscle belly of the sternocleidomastoid muscle (SCM) [48]; 2, the anterior scalene muscles, third portion of the muscle belly, parallel to the clavicular head of the SCM [48]; 3, the muscle belly of the splenius capitis muscles [49]; and 4, midpoint between the acromion and C7, parallel to the fibers of the descending upper trapezius muscle [50].

The EMG Works*®* version 4.1.5 (Delsys Inc.) software will be used to acquire and display the electromyographic signals during the acquisition. Raw electromyographic signals will be processed by a custom MATLAB*®* routine responsible for filtering them at a frequency band of 20–500 Hz, using a 4th order Butterworth filter, and the root mean square (RMS) of the filtered signal for the acquisition time will be calculated in each test.

### Statistical analysis

All statistical analyses will be performed by a professional statistician and they will be blinded to the allocation groups. An intention-to-treat analysis will be performed in order to verify the effect on the outcomes. Intention-to-treat analysis is the most indicated statistical analysis method in randomized clinical trials because it allows verification of the real efficacy of the intervention, and avoids an overly optimistic estimate that may result from removal of the non-adherent volunteers [51]. Mixed linear regression models will be performed for the primary and secondary outcomes to estimate between-group and within-group comparisons. “Time” and “group” will be considered as fixed effects and participants as a random effect (random intercept model). Baseline will be used as a covariate and the term “interaction time by group” will be included in the model to evaluate the interaction effect of differences between groups at each follow-up and within-group differences over time. Additionally, post hoc Bonferroni correction will be performed for group comparisons at each follow-up in the case of a significant “time” X “group” interaction.

In addition, to determine the clinical relevance of between-groups differences, Minimal Clinically Important Difference (MCID) calculations will be performed for the variables that do not have the MCID described in the literature, and the Effect Size (ES) will be calculated based on the distribution methods. Differences will be considered clinically relevant when they overcome the MID combined with an ES > 0.4, following the criteria suggested by Armijo-Olivo et al. [52]

For the missing data, as recommended by CONSORT [29], imputation occurs through a mixed effect regression model*.*

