**Methods:**

A two-armed, parallel-groups randomized controlled trial with 3 months of follow-up will be conducted. 42 individuals, both genders, aged between 18 and 55 years old with a medical diagnosis of migraine will be included. The intervention group will perform a protocol consisting of exercises for strengthening the muscles of the cervical spine. Participants within the sham ultrasound group will receive detuned ultrasound therapy in the upper trapezius muscle. Both groups will receive a weekly session for 8 weeks. The efficacy of each intervention will be measured by the frequency and intensity of migraine at a 3-months follow-up.

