### Study schedule

#### Screening

A prescreening will be conducted among individuals who expressed an interest in the study on social media. The basic criteria of their migraine will be queried (e.g., location, intensity, and type of headache), and those who apparently fit the characteristics of migraine will be referred to the neurologists. After confirming the diagnosis of migraine and the inclusion criteria, the volunteer will be invited to participate in the study. Those who accept the invitation will receive all pertinent information about the study and begin to fill a paper headache diary [9]. After 30 days, the volunteer will undergo evaluation 1, which will consist of the application of questionnaires and a physical examination, and at the end of evaluation 1 randomization will occur. Depending on patient availability, treatment will begin in the next few days. Follow-up will occur 1, 2, and 3 months after the end of treatment.

The study design, which covers the screening, evaluation, intervention, and follow-up procedures is summarized in Fig. 1.

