### Sample size

A sample size of 21 individuals on each group was the result of a calculation in which a level a significance (α) of 0.025 was adopted, with a power of 80%, a between-groups difference to be detected of 3.3 (SD = 3.1) days of headaches per month, and considering a loss of 20% at follow-up. The mean and standard deviation used in the sample size calculation were based on the reduction of the frequency of a gold standard pharmacologic treatment group for migraine management from a previous clinical trial [9]. For the primary outcome “headache intensity”, adopting the same parameters as the previous calculation, a sample size of 20 would be necessary to detect a between-groups difference of 1.52 (SD = 1.37) in the NPS, based on data from 4-week pharmacological treatment [53].

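### Tying the follow-up group comparisons to a significant time-by-group interaction, with baseline as a covariate, can withhold the 3-month comparison that the trial was sized for

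*Protocol article*

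**What the plan says.** All of the following is in the protocol article.

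- **Model (Statistical analysis).** Time and group "will be considered as fixed effects and participants as a random effect (random intercept model"). The section continues: "Baseline will be used as a covariate and the term" for the time-by-group interaction is added. The stated purpose of that term is "to evaluate the interaction effect of differences between groups at each follow-up and within-group differences over time".
- **Condition (Statistical analysis).** A "post hoc Bonferroni correction will be performed for group comparisons at each follow-up in the case of a significant" interaction. This is the only sentence that sets a test of the groups at individual follow-ups. The article gives no test level for the interaction.
- **Primary time point (Abstract, Methods).** "The efficacy of each intervention will be measured by the frequency and intensity of migraine at a 3-months follow-up".
- **Visits (Screening).** "Follow-up will occur 1, 2, and 3 months after the end of treatment".
- **Design basis (Sample size).** The calculation uses "a level a significance (α) of 0.025 was adopted, with a power of 80"%, and "a between-groups difference to be detected of 3.3 (SD = 3.1) days of headaches per month". This is a direct two-group difference, not an interaction.

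**The concern.** If baseline is a covariate, it is not a response row, and the time factor holds only the follow-ups. The time-by-group term then compares the group difference at one follow-up with the difference at another. A treatment that works equally well at 1, 2 and 3 months produces no interaction, and its whole effect sits in the group term. A statistician who follows the sentence literally stops at the non-significant interaction and does not make the 3-month comparison by which the abstract measures efficacy.

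The rule applies to both primary outcomes, frequency and intensity. It is also a stated decision rule that does not fit the design basis, so it is more than a detail left for a later document. Because the wording has more than one reading, the reading could be chosen after the data are seen.

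**Working it through.** **1. The plan's own figure.** Normal approximation, two-sided alpha 0.025, power 80%:

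n per arm = 2·SD²·(2.241 + 0.842)² / difference²

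- Frequency: 2 × 3.1² × 3.083² / 3.3² = 16.8, so 17. Allowing for 20% loss gives 17/0.8 = 21.3 (22), or 17 × 1.2 = 20.4 (21). The article states 21.
- Intensity: 2 × 1.37² × 3.083² / 1.52² = 15.4, so 16. 16/0.8 = 20. The article states 20.

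One-sided 0.025 gives 14 for frequency before loss (18 after) and does not reproduce the figure. The sample size is therefore that of a direct group contrast at two-sided 0.025.

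**2. Inputs for the check.**
- From the article: difference 3.3, SD 3.1, alpha 0.025, three follow-ups, and 21 × 0.8 = 16.8, about 17 analysed per arm.
- Assumed: equal correlation ρ of 0.3 to 0.7 between a person's visits, including baseline; interaction tested at 0.05; Bonferroni over three follow-ups, 0.025/3 = 0.0083.

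**3. What the interaction tests.** With post-baseline rows only, the random intercept and the baseline term are constant within a person and cancel from comparisons between visits. With d_k the group difference at follow-up k, the noncentrality of the interaction F test is

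λ = (n/2) · Σ(d_k − mean d)² / [SD²(1 − ρ)].

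- Steady benefit (3.3, 3.3, 3.3): the sum is 0, so λ = 0 for every ρ. The test rejects at its alpha level and no more often.
- Growing benefit (1.1, 2.2, 3.3): the sum is 1.1² + 0 + 1.1² = 2.42, and λ = 8.5 × 2.42 / [9.61(1 − ρ)] = 3.06, 4.28, 7.13 for ρ = 0.3, 0.5, 0.7. With 2 and 64 degrees of freedom, the interaction is significant in about 31%, 42% and 64% of trials.

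**4. The direct 3-month contrast, adjusted for baseline.** SE = 3.1·√(1 − ρ²)·√(2/17):

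| ρ | SE | 3.3/SE | Power at 0.025, normal approximation |
|---|---|---|---|
| 0.3 | 1.01 | 3.25 | 84% |
| 0.5 | 0.92 | 3.58 | 91% |
| 0.7 | 0.76 | 4.35 | 98% |

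Simulation, which also pays for estimating the variance and the baseline slope, gives about 80% at the low end and 88% at ρ = 0.5. The simulated range over ρ is about 80-98%.

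**5. The two paths compared by simulation (17 per arm).**

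| Benefit at months 1, 2, 3 | Significant at 3 months through the condition | Direct 3-month contrast |
|---|---|---|
| 3.3, 3.3, 3.3 | about 3-4% | about 80-98% |
| 1.1, 2.2, 3.3 | about 28-62% | about 81-97% |

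If the interaction is tested at 0.025 instead, success through the condition for the steady benefit falls to about 1.5%. A fourth post-baseline visit does not change the result.

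**6. The alternative reading, with baseline also a time level.** For a steady 3.3-day benefit (17 per arm; ρ = 0.3, 0.5, 0.7), the interaction is significant in about 76%, 90% and 99% of trials. The 3-month result is significant through it in about 64%, 82% and 96%. But baseline is then both response and covariate, and at ρ = 0.5 the model SE is about 0.83 against a true 0.93. With no treatment effect, the uncorrected 3-month contrast rejects in about 3.1-4.5% of trials at nominal 2.5%. With the condition and the Bonferroni correction both applied, it rejects in about 0.9-1.7%.

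**The case against.** - **The sentence does not say that comparisons are made only after a significant interaction.** It can be read as making just the Bonferroni correction conditional, and the same section says without condition that the models estimate between-group comparisons. This stands as a possible reading. But the article then specifies no 3-month test and no level for it, so the same edit is needed.
- **The model contains a group effect.** A reader might infer that the analysis would return no effect for a steady benefit. That goes too far: the average group effect has about 98-100% power in the baseline-adjusted simulations. However, it averages over visits, is not the 3-month comparison, and is not named as the primary test.
- **Baseline may also be a time level.** The mention of within-group differences over time allows this, and step 6 shows that the condition then has reasonable power. The article says covariate, though, and using baseline in both roles makes the standard error too small.
- **A reader might infer that this second reading inflates the type I error of the primary test.** It does not for the path as written, because the condition and the Bonferroni correction together hold the 3-month error below 2.5%. The excess concerns the uncorrected contrast and its confidence interval.
- **An exactly steady benefit is the worst case.** This is true, and the article states no time course. The growing benefit still loses much of the power.
- **The exact contrast may be left to an analysis plan.** An omission could be. This is a stated rule that does not match the stated time point and sample-size basis.

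**Conclusion.** The concern holds on the plain reading: baseline as covariate only, and follow-up comparisons conditional on the interaction. For a steady 3.3-day benefit, the chance of a significant 3-month result falls from about 80-98% to about 3-4%. For a growing benefit it falls from about 81-97% to about 28-62%. That the interaction is null under a steady benefit is algebra and needs no assumption about correlation. The percentages rest on 17 per arm, SD 3.1, an assumed equal correlation of 0.3-0.7 and an assumed interaction level of 0.05.

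The documents do not support saying that the trial could not show a steady benefit at all, that every reading fails, or that the conditional, corrected test exceeds its error rate. They do show that the rule, as worded, can withhold the comparison for which the trial was designed.

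**What to change.** In the Statistical analysis section:

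1. Remove the interaction condition.
2. State that the primary test of each primary outcome is the model-based between-group difference at the 3-month follow-up, tested at 0.025, always computed and always reported with its confidence interval.
3. State that baseline enters as a covariate only and not also as a response row.
4. Report the interaction and the other follow-ups as supportive.

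The cost is one or two sentences. No new data, visits or participants are needed, and the analysis then matches the contrast on which the sample size was based.

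### Bonferroni, and the 0.025 per primary outcome if it is a split of 0.05, are valid but less powerful than Holm's step-down at the same familywise error; the gain is about 5 to 7 points per primary outcome when both effects are real, and usually small for the follow-ups

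*Protocol article*

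**What the plan says.** The Outcomes section names two primary outcomes, migraine frequency and migraine intensity.

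The Statistical analysis section fits a mixed model with baseline as a covariate and a time-by-group term. It then says that "post hoc Bonferroni correction will be performed for group comparisons at each follow-up", but only if that interaction is significant. It gives no test level for the primary outcomes and no rule for combining them.

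The Sample size section says that "a level a significance (α) of 0.025 was adopted". Its inputs are "a between-groups difference to be detected of 3.3 (SD = 3.1) days of headaches per month" for frequency and, with the same parameters, "a between-groups difference of 1.52 (SD = 1.37) in the NPS" for intensity. The result is "A sample size of 21 individuals on each group", "considering a loss of 20% at follow-up".

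The Study schedule section places follow-ups at 1, 2 and 3 months after treatment ends. The Abstract measures efficacy at 3 months.

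**The concern.** Bonferroni compares every p-value in a family with the same reduced level. Holm compares the smallest p-value with that level and, if it passes, relaxes the level for the next. Holm controls the same familywise error without further assumptions and rejects everything that Bonferroni rejects. Where the aim is familywise control over two or three tests, Bonferroni therefore gives up some power for nothing in error control.

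This matters because the trial is small. After the planned loss about 17 participants per arm remain, and the hypothesis covers both frequency and intensity. The trial is thus planned for the case in which both effects are real, and that is where Holm helps. The point concerns only the correction procedure within a family of comparisons, not which comparisons belong to it.

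**Working it through.** **Inputs from the article.** Frequency: d = 3.3/3.1 = 1.065. Intensity: d = 1.52/1.37 = 1.109. Level 0.025, power 80%, loss 20%, 21 per arm. Completers: 21 × 0.8 = 16.8, taken as 17.

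**Assumptions not in the article.** The level is two-sided; familywise error is 0.05; correlation is 0 to 0.6 between the two outcomes and 0.5 to 0.7 between follow-ups; there are three follow-up comparisons.

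**1. Reproducing the sample size.** Formula: n per arm = 2(z₁₋α/₂ + z₀.₈)²/d².
- Frequency at two-sided 0.025: 16.78, and 16.78/0.8 = 20.98, so 21.
- Intensity: 15.44, rounded to 16, and 16/0.8 = 20.

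Both match. One-sided 0.025 gives 18 and 17 per arm and does not match. The figures therefore fit a two-sided 0.05 halved over two outcomes, although the article does not say so.

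**2. t-test power at 17 per arm.**

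| | at 0.025 | at 0.05 |
|---|---|---|
| Frequency | 0.770 | 0.853 |
| Intensity | 0.806 | 0.880 |

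**3. Two primary outcomes, correlation 0, by hand.** Under Holm an outcome is significant if its p ≤ 0.025, or if its p lies between 0.025 and 0.05 and the other outcome's p ≤ 0.025.
- Frequency: 0.770 + (0.853 − 0.770) × 0.806 = 0.837.
- Intensity: 0.806 + (0.880 − 0.806) × 0.770 = 0.863.
- Both, Bonferroni: 0.770 × 0.806 = 0.621.
- Both, Holm: 0.853 × 0.880 − 0.083 × 0.074 = 0.745.
- At least one, either method: 1 − 0.230 × 0.194 = 0.955.
- Frequency if intensity has no effect: gain 0.083 × 0.025 = 0.002.

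**4. Correlated outcomes.** Simulation with 40,000 trials per scenario, correlation 0 to 0.6:

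| | Bonferroni | Holm |
|---|---|---|
| Frequency | 77% | about 83% |
| Intensity | 80-81% | about 85-86% |
| Both | 62-68% | 74-78% |

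Familywise error under the global null is the same for both methods, about 0.045 to 0.050. If all 21 per arm are retained, the normal approximation (correlation 0 to 0.8) puts the gain at 2 to 4 points per outcome.

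**5. Follow-up comparisons, with the interaction condition applied.** Each test is at 0.05/3 under Bonferroni; the interaction test is at 0.05.
- *Constant d = 1.06.* Without the condition, month-3 power goes from 71-72% to 79-80%. With baseline as a covariate, however, a constant effect means no interaction. The condition is met in about 5% of trials, and overall month-3 power goes from 3.2-3.4% to 3.5-3.9%, about 0.5 points or less.
- *d = 1.4/1.2/1.06.* The condition is met in 13-18% of trials. Month-3 power goes from 6-10% to 8-13%, a gain of 2 to 3 points.
- *Waning at 100/70/40% of the planned effect.* The condition is met in 35-55% of trials. Within those, the second visit gains about 6 points and the third 4 to 7. Overall: 0.35 × 6 = 2.1 to 0.55 × 6 = 3.3 at the second visit, and 0.35 × 4 = 1.4 to 0.55 × 7 = 3.9 at the third.
- *Steep case, d = 1.8/1.4/1.06.* The condition is met in 45-68% of trials. Within those, month-3 power goes from 59-66% to 76-81%. Overall: 0.45 × 17 = 7.7 to 0.68 × 15 = 10.2 points. This needs a first-month effect 1.8/1.065 = 1.7 times the planned one.
- *Effect at one visit only.* Gain about zero.

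**The case against.** Bonferroni is valid, pre-specified and conservative, and the trial was sized for 0.025, so the cost of the correction was budgeted. It also gives matching simultaneous confidence intervals, which Holm does not give as simply. All of this stands, and it makes the point one of efficiency rather than error. The interval argument weighs less here, because the article judges clinical relevance by a minimal important difference together with an effect size above 0.4, not by adjusted intervals.

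The 0.025 appears only in the Sample size section. Reading it as an analysis rule, and as half of 0.05, is an inference. How the two primary outcomes are tested may be set out in an analysis plan that is not shown. That also stands, and the two-outcome figures depend on the inference. The Bonferroni step for the follow-ups is stated outright.

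Three stronger readings are tempting, and the document supports none of them.
- A reader might infer a general loss of 5 to 10 points. Per primary outcome the gain is about 5 to 7 points at 17 per arm, and only if both effects are real. The larger figures concern significance on both outcomes, which the article does not make its success criterion.
- A reader might infer gains of 8 to 11 points at month 3 by ignoring the interaction condition. With the condition applied, the same two scenarios (constant effect and 1.4/1.2/1.06) give about 0.5 and 2 to 3 points.
- A reader might blame Bonferroni for frequency having 77% power and not 80%. That gap comes from the normal approximation in the sample-size calculation. Holm happens to close it when the intensity effect is also real, but did not cause or target it.

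**Conclusion.** The point holds as a cheap improvement, not as an error or contradiction. For the two primary outcomes, at the plan's effects and 17 completers per arm, Holm adds about 6 points for frequency, about 5 for intensity and roughly 10 to 12 for both. These figures rest on two-sided 0.05 familywise error, t-tests, an assumed correlation of 0 to 0.6 and both planned effects being real. The chance of at least one significant outcome does not change, and the gain is about zero if only one effect is real.

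For the follow-up comparisons as the plan is written, the gain is small: about 0.5 points at month 3 under a constant effect and about 1 to 4 points at later visits under moderate waning. Of the scenarios examined, only one with an early effect well above the planned size gives more.

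**What to change.** In the Statistical analysis section, replace the post hoc Bonferroni correction with a Holm step-down correction for the group comparisons at each follow-up. Add a sentence that the two primary outcomes are tested by Holm at an overall two-sided 0.05: the smaller p-value against 0.025 and, if that is significant, the other against 0.05. Keep 0.025 in the sample size as the conservative first step, and say that this is its purpose.

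The cost is a sentence or two, written before unblinding, with no new data or participants. The small downside is that Holm has no equally simple simultaneous confidence intervals, so unadjusted or Bonferroni intervals should be reported beside the Holm-adjusted p-values and labelled as such.
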